#### Data Analysis

We plan to first examine univariate and bivariate statistics to evaluate distributional properties of outcome measures and to identify potentially relevant confounders and covariates. We will also evaluate psychometric properties (eg, internal consistency) of self-report multi-item measures of psychosocial variables. Where warranted, we will apply transformations (eg, natural log) to normalize distributions of outcome measures. We will examine main effects of and interactions among Phase (Baseline vs Intervention), Goal Type (Static vs Adaptive), and Reinforcement Type (Delayed vs Immediate) using a generalized linear mixed (ie, random effects or multilevel regression) modeling approach, with repeated assessments of PA (ie, both steps/day and minutes above various step/min cadence levels) treated as nested within persons. To minimize collinearity among interaction terms and constituent linear effects, we will use effect-coded indicators (ie, -1/1) as opposed to dummy coded (ie, 0/1) indicators for dichotomous predictors. In all models, we will account for (1) effects of covariates identified in preliminary analyses, (2) linear, quadratic, and cyclical (weekly, monthly) time effects, (3) random variation in person-level intercepts, and (4) autocorrelation among residuals. All analyses will be conducted using mixed modeling procedures in SAS 9.4 (eg, PROC MIXED, PROC GLIMMIX) and R (eg, lme4).

We will model the main effect of each intervention component (either Goal Type or Reinforcement Type) on changes in PA (steps/day and cadence) from baseline to 4 months via Intervention x Phase (Baseline vs Intervention) interactions. The interaction between interventions will be examined via a Goal Type x Reinforcement Type x Phase interaction effect, with planned contrasts comparing PA change in the Adaptive Goal + Immediate Reinforcement condition to PA change in the other groups. Secondary analyses will be dependent on the specific research question and the most appropriate statistical methods for the design.

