## Methods

### Overview

The WalkIT trial was a 2x2 factorial RCT conducted over 4 months. Following a 10-day baseline phase to assess usual PA levels measured by Fitbit Zip accelerometers, participants underwent simple randomization using a computerized random number generator for assignment into one of four treatment groups. Main effects of the treatment included Goal Type (adaptive vs static goals) and Reinforcement Type (immediate vs delayed reinforcement). In brief, adaptive goals and immediate reinforcement were based on a percentile-shaping algorithm that adjusted each participant’s goal up and down daily based on their previous nine valid observations (usually the last 9 days) of Fitbit-measured steps. Static goals were set to the recommended 10,000 steps per day and did not change over the course of the study. Participants in the immediate reinforcement group received praise feedback and one reward point each time they met a daily goal, whereas those in the delayed reinforcement group received monthly incentives. All participants received a walking intervention with semi-automated text message–based components. Researchers monitored the text message system for non-standard messages from participants (eg, when a participant asked a question, the research staff was notified), and staff responded through the system.

The Arizona State University Institutional Review Board approved the intervention trial and all the procedures used in data collection. The study is registered as a clinical trial (NCT02053259). See Multimedia Appendix 1 for the CONSORT EHEALTH checklist [27].

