#### Objectively Measured Physical Activity

Participants in all four groups received a commercially available accelerometer (Fitbit Zip, Fitbit Inc.) to wear for the 4-month duration of the study. Participants wore the accelerometer for at least 10 days prior to randomization to an intervention group and continued wearing for the remaining approximately 110 days. The Fitbit clips on clothing near the hip and has a small and unobtrusive form factor, thus accommodating various clothing styles to minimize non-wear. Participants were asked to wear the Fitbit during all waking hours (ie, at least 10 hours) every day for the duration of the study (ie, both the baseline and intervention phases), removing it for sleeping or in circumstances that might submerge it in water (eg, swimming). Fitbit accelerometers have excellent reliability and validity for measuring steps compared to direct observation and Actical accelerometers [32,33]. The Fitbit recorded steps and transmitted the data to the study team via the Internet to verify participants’ texted step reports. The accelerometer’s display was masked during baseline (to avoid participant reactivity) and then unmasked at randomization. Participants were also asked to sync their Fitbit each day using a personal computer connected to the Internet and the Fitbit sync dongle. Instructions on how to install the software were provided and demonstrated in the lab. The study team initiated and created study-managed accounts on the Fitbit website so participants were *not* able to access or view activity history, nutrition trackers, “badges” earned, social media interfaces, and other online tools that could have acted as potential confounders. To further limit access to the Fitbit website, we did not allow participants to sync their Fitbit using Fitbit’s mobile phone app because this required logging into the study-managed account. Fitbit, Inc. allowed researcher access to their Application Programming Interface (API) but otherwise was not involved with this project.

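### The Group x Phase model with a free baseline mean in every arm is in effect a change-score test: valid, but less precise than a baseline-adjusted analysis by an amount the article does not let us fix

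*Protocol article*

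**What the plan says.** The Overview in Methods describes the sequence "Following a 10-day baseline phase to assess usual PA levels measured by Fitbit Zip accelerometers", then simple randomisation to four groups. Under Objectively Measured Physical Activity, participants wore the device "for at least 10 days prior to randomization to an intervention group and continued wearing for the remaining approximately 110 days", with the display masked until randomisation.

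The Data Analysis section puts all repeated activity values, baseline days included, into one mixed model, "treated as nested within persons". Its fixed part is given as "We will examine main effects of and interactions among Phase (Baseline vs Intervention), Goal Type (Static vs Adaptive), and Reinforcement Type (Delayed vs Immediate"). The effect of each component on change is tested "via Intervention x Phase (Baseline vs Intervention) interactions", and the joint effect by the three-way term, "with planned contrasts comparing PA change in the Adaptive Goal + Immediate Reinforcement condition to PA change in the other groups". Dichotomous predictors are effect-coded -1/1. The model also accounts for "effects of covariates identified in preliminary analyses", time trends, and "random variation in person-level intercepts, and (4) autocorrelation among residuals". Baseline steps are not named as a covariate, and baseline means are not constrained to be equal across arms.

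**The concern.** Because the whole baseline is recorded before allocation, the arms share one expected baseline mean by design. The planned model nevertheless spends three terms (Goal, Reinforcement, Goal x Reinforcement) on estimating baseline differences between arms. The Phase interactions then subtract each arm's observed baseline in full, including its sampling noise. A baseline-adjusted analysis subtracts only the part of the baseline that predicts follow-up.

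The stake is the standard error of both primary contrasts and of the interaction. The Power and Sample Size section assumes effects as small as 300 steps/day for Reinforcement x Phase and 150 for the three-way term, with about 80 completers, so precision is scarce there.

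**Working it through.** **The plan's own figure.** 80 completers / (1 - 0.20) = 100, so the attrition step reproduces. The power cannot be reproduced, because the article states no SD, ICC, autocorrelation, alpha or sidedness. As a guide (two-sided 0.05 assumed, 40 v 40), 80% power for 800 steps/day needs an SD of change of 800 / [(1.960 + 0.842) x sqrt(2/40)] = about 1,277. With that SD, 300 steps/day has about 18% power.

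**Is the planned test a change score?** With complete data, an identity link and independent residuals, the Goal x Phase estimate equals the difference in mean change exactly. A person-day generalised least squares (GLS) check gave 0.232644 for both. With AR(1) = 0.3 it is a slightly reweighted change contrast (0.2141 v 0.2124).

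**Where the noise sits.** With independent residuals, the 10 baseline days supply (1/10) / (1/10 + 1/110) = 92% of the within-person noise in the change.

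**Formulas.** From the article: 10 baseline days and 110 intervention days. Assumed: between-person SD sb, day-to-day SD sw, AR(1) correlation rho, and SD of true individual response tau, uncorrelated with baseline level.

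- Vb = sb² + sw² x a(10)
- Vi = sb² + tau² + sw² x a(110)
- C = sb² (the small residual correlation across the phase boundary is ignored)
- a(n) = [n + 2 x sum over k of (n - k) rho^k] / n², the variance factor for a mean of n AR(1) days
- Var(change) = Vb + Vi - 2C
- Var(adjusted) = Vi - C²/Vb, with optimal slope C/Vb

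**One worked case** (sb 2,000, sw 3,190, rho 0.3, tau 1,000): a(10) = 0.1735 and a(110) = 0.0168.

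- Vb = 4,000,000 + 1,765,243 = 5,765,243
- Vi = 4,000,000 + 1,000,000 + 170,774 = 5,170,774
- Slope = 4,000,000 / 5,765,243 = 0.69, where the change score uses 1
- Var(change) = 2.94 million; Var(adjusted) = 2.40 million; ratio 0.816

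Person-day GLS with 20 completers per cell gives a standard error for Goal x Phase of 378 steps as planned and 343 with a common baseline mean. Linear and quadratic time terms common to all arms do not change these values.

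**Range.** Ratio of adjusted to planned variance, over sb 1,500-2,500, sw 2,500-3,190 and rho 0-0.3:

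| Response SD (tau) | Lowest ratio | Highest ratio | At 2,000 / 3,190 / 0.3 |
|---|---|---|---|
| 0 | 0.60 | 0.92 | 0.72 |
| 1,000 | 0.74 | 0.97 | 0.82 |
| 2,000 | 0.87 | 0.99 | 0.91 |

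If response also correlates +0.3 with baseline level, the last column becomes 0.92 at tau 1,000 and 0.99 at tau 2,000. A negative correlation would enlarge the gain.

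**Coding check.** With Phase coded -1/1, deleting Goal, Reinforcement and Goal x Reinforcement while keeping their Phase interactions forces equal and opposite arm differences at baseline and intervention. With equal true baselines and a true Goal x Phase effect of 800, GLS expectations are:

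| sb / sw / rho / tau | Full model as planned | Terms deleted, Phase -1/1 | Terms deleted, Phase 0/1 |
|---|---|---|---|
| 2,000 / 3,190 / 0.3 / 1,000 | 800 | 823 | 800 |
| 2,000 / 3,190 / 0.3 / 0 | 800 | 869 | 800 |
| 1,500 / 3,190 / 0.3 / 0 | 800 | 913 | 800 |
| 2,500 / 2,500 / 0 / 0 | 800 | 818 | 800 |

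**The case against.** The strongest reply is that nothing here is an error. A Group x Phase mixed model is standard, matches the stated aim of comparing change, and targets the same interactions as the sample-size simulations. That stands. A reader might infer that the primary test is biased, or that N=100 is too small because of this choice. The documents support neither: the planned estimate is unbiased, and the simulations were built on the same Phase interactions.

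A second reply is that the size is unknown. That also stands. It is tempting to present one case, such as the 0.82 above, as the expected gain, but that depends on fixing the response SD at 1,000, which nothing in the article supports. Nor does excluding people who reach 10,000 steps on five days a week establish a larger gain, since its effect on the between-person spread is not quantified. The baseline is noisy only relative to the 110-day mean: with independent residuals and an ICC of 0.3 to 0.7, the reliability of a 10-day mean is 0.81 to 0.96.

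A third reply is that the open covariate clause could bring in baseline steps. This does not help. A person-level covariate without a Phase interaction leaves the within-person Phase contrast essentially unchanged.

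**Conclusion.** The point holds as one of efficiency. The article specifies a valid and unbiased test that is less precise than a baseline-adjusted one whenever the optimal baseline slope is below 1. Under the assumed ranges, with response uncorrelated with baseline, the adjusted variance is about 0.60 to 0.99 of the planned variance. That runs from a substantial gain to almost none, and the documents cannot narrow it. The gain fades if individual response varies widely or correlates positively with baseline level. Exact equivalence to a change score needs complete data and independent residuals; otherwise it is approximate. The change is worth making because the baseline data are already collected, but it improves the plan and does not correct a mistake in it.

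**What to change.** For the primary contrasts and the interaction, specify one of the following.

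- (a) Model intervention-phase days only, with each person's baseline mean steps as a covariate and Goal, Reinforcement and Goal x Reinforcement as the effects of interest.
- (b) Fit a constrained longitudinal model with Phase coded 0 at baseline and 1 in the intervention phase, no group terms at baseline, Phase and all Group x Phase terms kept (including the three-way term), and a random intercept plus a random Phase effect.

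Do not simply delete the three group terms while Phase stays coded -1/1. The two options need not agree exactly when days are missing, which the Missing Data section anticipates, so name one as primary.

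The cost is recoding Phase and a small change to the model statement; no further data are needed. The Results section says analyses were still in progress, so the choice should be fixed before outcomes are compared by arm.

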### Statistical Analysis

#### Power and Sample Size Determination

To estimate the sample size required to test the main aim of changes to steps/day, we conducted a set of simulations using a SAS macro developed by Psioda [50] and effect size estimates derived from findings reported by Adams et al [16]. Across the simulation runs, we varied the number of participants (Ns of 60-96), the magnitude of change from baseline to intervention Phase (1200 vs 1600 steps/day), magnitude of Goal Type (Static vs Adaptive) x Phase interaction effect (800 vs 1200 steps/day between-group difference in the magnitude of the Phase effect; compare to 1130 steps/day difference reported by Adams et al [16]), magnitude of Reinforcement Schedule (Delayed vs Immediate) x Phase interaction (300 vs 500 steps/day between-group difference in the magnitude of the Phase effect), and the Goal x Reinforcement x Phase interaction (150 vs 300 steps/day difference in Phase effect over and above the main effects and 2-way interaction effects). The simulations revealed that under the most conservative sets of assumptions (ie, sets comprising combinations of the smallest effect magnitudes) and an assumed attrition rate of 20%, a total initial sample size of N=100 participants (n=25 per group) would be required to have power of .80 or greater to detect hypothesized interaction effects.

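### The models listed for all analyses name no person-level random Phase effect, so the Intervention x Phase tests are anti-conservative to the extent that individuals differ in lasting change

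*Protocol article*

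**What the plan says.** Under Data Analysis, daily physical activity measures are "treated as nested within persons" in a mixed model. The effect of each component is estimated "via Intervention x Phase (Baseline vs Intervention) interactions", and the joint effect by a Goal Type x Reinforcement Type x Phase interaction.

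The model content is given as a numbered list that opens "In all models, we will account for (1) effects of covariates identified in preliminary analyses", continues with linear, quadratic and cyclical time effects, and closes with "3) random variation in person-level intercepts, and (4) autocorrelation among residuals". The article mentions no random slope, random Phase effect or robust standard error.

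The data per person are unbalanced between phases. The Methods Overview has "Following a 10-day baseline phase to assess usual PA levels measured by Fitbit Zip accelerometers", after which participants "continued wearing for the remaining approximately 110 days". Power and Sample Size Determination arrives at "a total initial sample size of N=100 participants (n=25 per group"), with 20% attrition assumed, for "power of .80 or greater to detect hypothesized interaction effects". It gives effect sizes but no standard deviation, autocorrelation or variance of individual change.

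**The concern.** Goal Type and Reinforcement Type were assigned to persons, not to days. A factor-by-Phase interaction therefore asks whether the average change differs between groups of persons, and its error term must include how much persons in the same group differ in change. The listed random intercept describes differences in level, which subtract out of a within-person change. With no further person-level term, the model behaves as if everyone in a cell changed by the same amount, apart from day-to-day noise.

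If that is untrue, standard errors are understated and the error runs towards false claims of a component effect or of synergy. The article's own rationale suggests that it is untrue. Goal Setting says that the static goal may exceed some participants' abilities. Limitations says that four months may be too short for some. Recruitment and Setting describes rolling enrolment from February to August, with average highs of 41.2°C in July and 18.9°C in December, so the baseline-to-intervention contrast in weather depends on when a person joined.

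**Working it through.** **1. The plan's own figure.** With 20% attrition, 100 x 0.8 = 80 completers, or 40 per level of each factor. That step reproduces. The power cannot be reproduced, because no variances and no alpha are given. It can be inverted (two-sided 0.05, 40 v 40):

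largest SD of change = effect / [(1.960 + 0.842) x √(2/40)]

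- 800 steps/day: 800 / 0.6265 = 1,277
- 300 steps/day: 479
- 150 steps/day: 239 (120 if the 150 is a difference of differences)

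This is the SD of each participant's observed mean change, day-to-day noise included.

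**2. True standard error.** Let σ be the daily residual SD, ρ its AR(1) autocorrelation and τ the SD of lasting individual change. A person's change has variance τ² + ω², where ω² is the noise part, and the intercept has dropped out. For 40 v 40,

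true SE² = (τ² + ω²)(1/40 + 1/40) = (τ² + ω²)/20.

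Hand check with independent days: σ = 2,500 gives ω² = 6,250,000 x (1/10 + 1/110) = 681,818. At τ = 0 the SE is √34,091 = 185. At τ = 1,000 it is √(1,681,818/20) = 290, while the listed model reports 188. The true type I error is then 2[1 − Φ(1.96 x 188/290)], or about 0.20.

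**3. With autocorrelation.** The listed model (random intercept plus AR(1)) was evaluated at its expected-likelihood optimum, so that the autocorrelation term could absorb whatever it can. All variances are assumptions, with an intercept SD of 2,000. Fixed time effects, which are shared by all groups, were left out. Cells show model SE / true SE in steps/day, then type I error at a nominal 5%.

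| τ | σ 2,500, ρ 0.2 | σ 2,500, ρ 0.4 | σ 3,500, ρ 0.2 | σ 3,500, ρ 0.4 |
|---|---|---|---|---|
| 0 | 220 / 220, 5.0% | 259 / 259, 5.0% | 308 / 308, 5.0% | 363 / 363, 5.0% |
| 500 | 221 / 247, 8.0% | 260 / 282, 7.1% | 308 / 328, 6.5% | 364 / 380, 6.1% |
| 1,000 | 223 / 314, 16.3% | 262 / 342, 13.3% | 310 / 381, 11.0% | 365 / 426, 9.3% |
| 1,500 | 227 / 401, 26.8% | 266 / 424, 21.8% | 313 / 455, 17.8% | 368 / 494, 14.4% |
| 2,000 | 232 / 498, 36.1% | 272 / 517, 30.3% | 317 / 543, 25.3% | 372 / 576, 20.6% |

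**4. Why AR(1) residuals do not help.** A lasting shift does not decay over days. In the first column, as τ goes from 0 to 2,000, the fitted ρ moves only from 0.20 to 0.24. The fitted intercept SD rises from 2,000 to 2,708, so much of the extra variation goes into the term that cancels from the interaction.

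**5. Cross-check by simulation.** With σ = 3,000 and ρ = 0.25, the same calculation gives 5.0%, 6.9%, 12.5%, 20.4% and 28.6% for τ = 0, 500, 1,000, 1,500 and 2,000. Simulated data fitted by maximum likelihood (150 replicates x 3 tests per setting, τ = 500 not run) gave 3.8%, 11.8%, 20.2% and 28.4% at 0, 1,000, 1,500 and 2,000. Adding a random Phase effect at τ = 1,500 brought the rate to 4.2% (80 replicates).

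**6. What it means for inference.** At σ = 2,500, ρ = 0.2 and τ = 1,000, a nominal 95% interval covers 83.7%. Power for 800 steps/day is 0.72 with the correct SE, against an apparent 0.95 from the model SE.

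**The case against.** The strongest reply is that the list is not closed. It says what every model will include. It does not say that nothing else will be included, and the surrounding text speaks generally of multilevel modelling. In a condensed article, further random effects and the degrees-of-freedom method may sit in an analysis plan that is not shown. This stands against reading the article as forbidding a random Phase effect. It does not dispose of the point: the article is not silent on the covariance, but names a random effect and a residual structure for all models, and an analyst who follows that list obtains the understated standard error.

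A reader might also infer that the intervals are far too narrow. The documents do not support that, since they give no variances. The understatement could be slight. Baseline noise also limits it: in a simple difference of means with independent days, (1/10)/(1/10 + 1/110) = 92% of the day-to-day error variance comes from the 10 baseline days, so the model does not simply credit 110 intervention days as independent evidence on the group effect.

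Nor does the article call all three interactions primary. The hypothesis under Purpose and Aims concerns the two components, and the three-way term is only to be examined. Finally, data collection is complete, so re-running the power simulation cannot change the sample size.

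**Conclusion.** The point holds in conditional form. The listed structure omits the person-level variation in change that the factor-by-Phase tests need, and residual autocorrelation does not replace it. The direction is certain whenever individuals differ in lasting change; the size is not known. Under the assumed residual SDs of 2,500 to 3,500 and autocorrelations of 0.2 to 0.4, the true type I error is about 6–8% at an SD of change of 500 steps/day, 9–16% at 1,000 and 21–36% at 2,000, and exactly nominal at zero. These figures rest on 80 completers in balanced groups with complete 10 + 110 day records, and on variances that the article does not supply. They show what could happen, not what did. The two component tests, the three-way interaction and the planned contrasts are all exposed.

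**What to change.** Add a person-level random Phase effect to the Goal x Phase, Reinforcement x Phase and three-way models, keeping the random intercept and the autocorrelated residuals. Alternatively, use person-clustered robust standard errors. Check the result against a between-person analysis: one mean change per participant, regressed on Goal Type, Reinforcement Type and their product. State the SD of individual change that the power simulation assumed, so that readers can judge the claimed power.

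The cost is one extra random term in software already named in the article, with no change to trial conduct. The article reports that data cleaning and preliminary analyses were still in progress. Intervals will be wider but correct, and real power may prove lower than the apparent figure. If the estimated variance of change is near zero, results will barely move.
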